## Abstract

**Background:**

Breast augmentation with silicone implants is one of the most frequently performed cosmetic surgeries worldwide. Surgical site infection (SSI) remains an important complication of this procedure. One of the most important risk factors for SSI is the presence of microorganisms on the skin surrounding the wound. Guidelines by the Centers for Disease Control (CDC) recommend that surgical wounds be covered with a sterile dressing for 24 to 48 hours. However, a recent study showed that the application of a dressing for six days after breast reduction reduced wound colonization by coagulase-negative staphylococci.

**Methods/Design:**

A randomized clinical trial was designed to assess two protocols of postoperative wound care to determine how the application duration of the postoperative dressing influences wound colonization in patients undergoing breast augmentation with silicone implants. Women aged between 18 and 60 years who are candidates for breast augmentation with silicone implants will be randomly allocated to group I (n = 48), in which the dressing will be removed on the first postoperative day, or group II (n = 48), in which the dressing will be removed on the sixth postoperative day. Cutaneous colonization will be assessed by cultures of samples of skin flora taken from the wound region. The incidence of SSI, using standardized CDC criteria, and the perceptions of patients towards the dressing will be secondary outcomes.

**Discussion:**

An important component of SSI prevention is to minimize all possible risk factors, and the application of postoperative dressing plays a key role in this endeavor. The results of this clinical trial may help to standardize postoperative wound care after breast augmentation with silicone implants.

**Trial registration:**

This trial was registered on 12 March 2012 with ClinicalTrials.gov (identifier: NCT01553604).

## Background

The popularity of breast augmentation with silicone implants has grown exponentially in the last decade. Since 2007, this operation is one of the most frequently performed cosmetic surgeries worldwide. In 2012, over 330,000 new breast augmentations were performed in the United States alone [1]. Despite advances in the surgical technique of breast augmentation and the technology for manufacturing breast implants, surgical site infection (SSI) remains an important complication of this procedure [2,3]. SSI increases morbidity, financial and personal costs, and the possibility of operative failure, as the implant may need to be removed to treat the infection [4].

The risk of postoperative SSI in primary augmentation mammoplasty with silicone implants is estimated to be between 0.1 and 2.5% [2,4-10]. These low rates of SSI make correlations with risk factors or specific interventions difficult, as very large sample sizes are required to determine statistically significant correlations [11]. However, due to the severity of the consequences of implant-related SSI, any contribution towards understanding these risk factors will aid in the development of strategies for preventing infection and improving surgical outcomes [12].

One of the most important risk factors for SSI is the presence of microorganisms on the skin surrounding the wound [4,11,13,14]. This risk increases when alloplastic material is used [4]. The ability of endogenous skin bacteria to colonize mammary prostheses has been demonstrated *in vitro* [15]. Bacteria from the endogenous flora or external sources of contamination may adhere to the implant and form an extracellular polysaccharide-rich matrix or biofilm, which surrounds the implant [16]. Bacteria aggregate and adhere to this extracellular matrix, enabling them to evade the host immune response and resist systemic antibiotics. Biofilm formation facilitates plasmid transfer among the bacteria, leading to highly virulent organisms. The minimum inhibitory concentration of antibiotics is 1,000 times greater for biofilms than for planktonic bacteria [17]. The seeding of a foreign body and the subsequent formation of a biofilm are not only difficult to diagnose, but may be very difficult to treat, especially with routine antibiotics [18]. Studies have suggested that chronic subclinical infection related to biofilms on implants may be associated with symptomatic capsular contracture, which is the leading cause of reoperation in mammary prosthetic surgery [19-24].

SSIs are related to preoperative factors (such as patient selection), intraoperative factors (such as type of surgery), and postoperative factors. Surgical wound management during the postoperative period greatly influences the risk of SSI because the skin incision serves as a gateway for microorganisms [4,20,25,26]. Bacteria can access the operative site via the incision. They may multiply and invade tissues to cause infection, depending on their number and pathogenic interaction with the host immune system [19]. However, few studies have justified the normalization of this period [26].

Care of surgical incisions has long been practiced. The use of dressings has been documented for over 4,000 years, but Joseph Lister introduced the concept of antisepsis only in the nineteenth century. The ideal dressing should protect the wound from trauma and contamination, absorb secretions, and provide the necessary compression to minimize edema and obliterate any dead space. Furthermore, the dressing covers unsightly operative wounds, thereby improving the psychological wellbeing of the patient [26,27].

The standardization of postoperative wound dressings, including those used after breast surgery, has been based on scarce and empirical evidence [28,29]. Different materials and techniques for the application of new dressings have been developed, however, conventional gauze-based dressings are still used very often [30]. A systematic review failed to prove the superiority of any one type of dressing over another type, or no dressing, and suggested a need for well-designed clinical trials to determine the ideal application time for postoperative wound dressings, an issue that remains controversial [31].

Guidelines by the Centers for Disease Control (CDC) recommend that surgical wounds be covered with a sterile dressing for 24 to 48 hours [25]. Subsequent postoperative care should be individualized; there is no ideal home-care protocol. At present, the care of postoperative wounds is not standardized and is based on the individual experience of each surgeon [25,26]. A recent study by Veiga-Filho *et al*. [32] showed that the application of a dressing for six days after breast reduction reduced wound colonization by coagulase-negative staphylococci. These authors also demonstrated that patients preferred to retain the same dressing for six days and considered this method to be safe [32].

## Methods/Design

### Study aims

A randomized clinical trial was designed to assess two protocols of postoperative wound care to determine how the application duration of the postoperative dressing influences wound colonization in patients undergoing breast augmentation with silicone implants. The secondary aims are to determine the SSI rates and the perceptions of the patients regarding the comfort, convenience and safety of the postoperative dressing. The trial will be conducted in a double-blinded manner in a university hospital in Brazil (Hospital das Clínicas Samuel Libânio, Universidade do Vale do Sapucaí). This trial has been registered at Clinicaltrials.gov (identifier: NCT01553604).

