### Group assignment, randomization and allocation concealment

Patients will be randomly allocated to group I (n = 48), in which the dressing will be removed on the first postoperative day, or group II (n = 48), in which the dressing will be removed on the sixth postoperative day. Allocation will be determined by a random, computer-generated sequence (Bioestat 5.0, Instituto Mamirauá, Belém, PA, Brazil). An opaque envelope with the patient number will be opened on the first postoperative day to reveal the allocation of the patient.

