### Procedures and interventions

Patients will be instructed to bathe before surgery with a 4% chlorhexidine-based detergent (Rioquímica Indústria Farmacêutica Ltda., São José do Rio Preto, Brazil) [33]. In the operating room, antisepsis of the surgical site will be performed with a 0.5% chlorhexidine solution in alcohol (Rioquímica Indústria Farmacêutica Ltda., São José do Rio Preto, Brazil) [34]. The nipple areola complexes will remain uncovered during the operation; sterile tapes will not be used to cover them, since this is not the standardized procedure in our hospital. Patients will undergo breast augmentation under general anesthesia. All patients will receive prophylactic antibiotics (cefazolin - União Química Farmacêutica Nacional S.A., São Paulo, Brazil) [35].

The surgical approach will be via the inframammary fold. Implants (Silimed Indústria de Implantes Ltda., Rio de Janeiro, Brazil) will be placed in the subglandular, submuscular or subfascial position, depending on which is the best course of action for a given patient. The surgical site will be cleaned with sterile saline after the surgery. A sample of skin flora will be obtained for semiquantitative culture before the application of a dressing over the surgical incision.

The dressing will consist of four layers of cotton gauze, covered with micropore tape. The surgical team will not know to which group the patient belongs. On the first postoperative day, the allocation envelopes will be opened. If the patient is allocated to group I, the dressing will be removed, and a sample will be harvested for culture. The patient will be instructed to return to their normal personal hygiene routine and return on the sixth day for reassessment and collection of samples for culture. If the patient is allocated to group II, she will be instructed to not wet the bandage for six days, when it will be removed and a sample will be harvested for culture. Thus, samples of the skin flora will be obtained in the operating room just before placement of the dressing and after removal of the dressing. Additional samples will be obtained on the sixth postoperative day from patients in group I.

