### Method of sample collection

A sterile fenestrated paper field with a standard 5 cm per 10 cm area will be placed over the surgical wound on the right breast. A sterile swab soaked in sterile saline will be passed across the predetermined area in a standardized manner. This swab will be placed in a sterile tube containing 1.0 ml of sterile saline and immediately transferred to the laboratory.

Culture methodsStandard culture methods will be used for the identification of microorganisms [36]. Aliquots of 0.2 ml from each sample will be plated on agar medium hypertonic mannitol (HiMedia Laboratories Pvt. Ltd., Mumbai, India) to culture *Staphylococcus* sp., on blood agar (HiMedia Laboratories Pvt. Ltd., Mumbai, India) to identify hemolytic colonies, on eosin-methylene blue agar (HiMedia Laboratories Pvt. Ltd., Mumbai, India) to identify *Enterobacteriaceae*, and on Sabouraud agar supplemented with chloramphenicol (HiMedia Laboratories Pvt. Ltd., Mumbai, India) (0.05 mg/ml) to detect fungi. The plates will be incubated in an aerobic atmosphere at 37°C. After 48 hours, a microbiologist will assess the plates. The lab technicians and microbiologist will not know which group each sample belongs to.

Culture results will be expressed as CFUs per plate. When a result exceeds 300 CFUs, it will be recorded as ‘>300 CFU/plate’. Staphylococci will be identified as coagulase-negative staphylococci or *Staphylococcus aureus*, on the basis of the results of Gram staining, the presence of hemolysis, and the results of the coagulase test.

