### Assessment of postoperative infections and dressing duration

Patients will be evaluated weekly for four weeks, and then re-evaluated at six months and one year after the operation. The CDC definition and classification of SSIs will be used. As the surgery involves the implantation of prostheses, an SSI is defined as an infection that occurs within one year after the surgery [37]. The patients will use a five-point scale to classify the dressing in terms of comfort, practicality and safety. This assessment will be done at the postoperative week two visit for each patient.

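### The unqualified double-blind label conflicts with the procedures: patients know their arm from postoperative day 1, and masking afterwards is stated only for the laboratory

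*Protocol article*

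**What the plan says.** Under Study aims, the protocol article states: "The trial will be conducted in a double-blinded manner". That sentence does not say which parties are blinded.

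The other sections describe masking piece by piece:

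- **Group assignment, randomization and allocation concealment:** an opaque envelope "will be opened on the first postoperative day to reveal the allocation of the patient".
- **Procedures and interventions:** "The surgical team will not know to which group the patient belongs". The next sentence begins the unmasking: "On the first postoperative day, the allocation envelopes will be opened". Then: "If the patient is allocated to group I, the dressing will be removed, and a sample will be harvested for culture". A group I patient goes back to her usual hygiene. A group II patient is told to keep the bandage dry until it comes off on day 6. On sampling: "Additional samples will be obtained on the sixth postoperative day from patients in group I".
- **Method of sample collection:** "The lab technicians and microbiologist will not know which group each sample belongs to". The coding of tubes is not described.
- **Assessment of postoperative infections and dressing duration:** "The patients will use a five-point scale to classify the dressing in terms of comfort, practicality and safety". The rating takes place at the week-two visit. SSI is judged by CDC criteria at weekly visits for four weeks, then at six months and one year. Neither the assessor nor any masking of the assessor is mentioned.

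**The concern.** Readers usually take an unqualified double-blind claim to mean that at least the patients, and those who treat or assess them, do not know the allocation. Here the two arms differ in something the patient sees and is told about, and the difference starts on day 1. The claim cannot be true of patients.

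Three outcomes are affected to different degrees.

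- **Patient perception** is rated by people who know their arm. The Background reports an earlier breast-reduction study in which patients preferred the six-day dressing and considered it safe, so neutral expectations cannot be assumed.
- **SSI** involves clinical judgement and will be rare. If the article's 0.1 to 2.5% is read as a per-patient risk, 96 patients give 96 × 0.001 ≈ 0.1 to 96 × 0.025 = 2.4 expected infections. A single classification could change the comparison, so whether the assessor knows the arm matters.
- **CFU counts**, the primary outcome, are read by a laboratory declared masked. The sampling schedule is uneven between arms, which makes that masking depend on how tubes are labelled.

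**Working it through.** No figure in the plan is at issue, so the check sets the statements side by side, party by party, and adds a count of samples.

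**Patients.** The envelope is opened on day 1. One group has the dressing taken off that day; the other is instructed to keep it dry until day 6. Each patient therefore knows her assigned care from day 1. The rating comes at week two, after this. For patients the conflict with the label is direct and needs no further assumption.

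**Surgical team.** The only masking sentence stands immediately before the sentence that opens the envelopes. It plainly covers the operation and the placing of the dressing. Nothing says that it continues afterwards. Patients come from the private practices of three of the investigators (Inclusion and exclusion criteria), and anyone who sees the wound between day 1 and day 6 can tell the arm. Against that, the article does not say who opens the envelope, removes the dressing, takes the swabs or conducts follow-up. Unmasking of surgeons from day 1 is a likely inference and not a stated fact.

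**SSI assessors.** No masking is stated. Masking is possible, however: after day 6 neither arm wears the dressing, so a visit after that day does not itself reveal the arm.

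**Laboratory.** Masking is declared. The samples planned under Procedures and interventions are:

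| | Operating room | Day 1 | Day 6 | Per patient | Total |
|---|---|---|---|---|---|
| Group I (n = 48) | yes | yes | yes | 3 | 48 × 3 = 144 |
| Group II (n = 48) | yes | no | yes | 2 | 48 × 2 = 96 |

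The overall total is 144 + 96 = 240, and all 48 day-1 samples come from group I. What this can reveal is limited:

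1. The operating-room sample is taken before the envelope is opened, so its reading cannot be influenced by allocation.
2. The Statistical analysis section compares the arms only before the dressing and at day 6. Recognising a day-1 plate does not by itself affect that comparison.
3. Both arms are swabbed on day 6, so a day-6 date alone does not separate them.
4. The arm behind a day-6 plate is revealed only if that tube can be linked to the presence or absence of a day-1 tube from the same patient, for example by a patient number. The article describes no such link and no coding that would prevent it.

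**What can still be changed.** Trial status reports 69 patients enrolled and operated on, out of 96 planned. That leaves 96 − 69 = 27 patients for whom every swab can still be coded.

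**The case against.** The strongest defence is that the article names two masked parties, the surgical team and the laboratory, and that these are what the word double refers to. The primary outcome is a laboratory count with declared masked reading. Patients rate a dressing they wore, so no reader would suppose that they did not know how long they wore it. Tube coding and the identity of the SSI assessor are details that a condensed article commonly leaves to the full protocol.

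Much of this stands. Masking patients is not possible with this intervention, so an open-label perception outcome is no design fault; the fault is in the description. The lack of coding detail is not a defect in itself. The defence does not rescue the label, though. The surgical team's masking is stated only ahead of the day-1 opening, which precedes the day-6 comparison and both secondary outcomes. An unqualified claim still covers patients in ordinary reading.

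A reader might infer three stronger things, none of which the document supports:

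- *The extra swab unmasks the laboratory, so the primary result is compromised.* The article says the opposite about the laboratory, and unmasking would need a link between tubes that is nowhere described.
- *All treating surgeons know the arm from day 1.* This is plausible, but who opens envelopes and who follows patients is not stated.
- *SSI assessment is unblinded.* Masking is unstated, which is not the same. A masked assessor is compatible with the text.

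**Conclusion.** The double-blind label is wrong as written. For patients this is certain: all 96 planned patients know their arm from day 1, and the comfort, practicality and safety ratings are open-label. For the surgical team and for SSI assessment, the label has no support after the day-1 opening. Unmasking there is likely on the assumption that the recruiting surgeons also follow their own patients. For the laboratory, masking is declared and should be accepted, with a conditional weakness: it could fail for day-6 plates if tubes can be linked by patient across days.

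The size and direction of any resulting bias cannot be derived from the document. The design need not change; its description should be corrected, with two inexpensive safeguards added.

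**What to change.** 1. Replace the label under Study aims with a statement by party: patients unmasked from postoperative day 1; surgical team masked until the envelope is opened on day 1; laboratory reading masked.
2. Interpret and report the perception results as open-label. Do the same for SSI unless its assessor is masked.
3. Label the remaining swabs with random specimen codes that show neither patient nor postoperative day, with the linking list kept outside the laboratory.
4. Where feasible, have SSI at visits after day 6 scored by an existing investigator who does not know the allocation. Otherwise state that SSI is assessed unblinded.

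The cost is small: a less favourable design label, a rewritten sentence and a coding list. The masked SSI scoring needs some rearrangement of who sees whom, and it works only if patients do not disclose their arm. Coding is not retrospective. It covers the 27 patients not yet enrolled at the reported status and any swabs still outstanding among the 69 already operated on; for samples already read, the report should say how tubes were labelled. SSI follow-up lasts one year, so masked scoring can still reach visits not yet held.

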### Ethical issues

The Ethical Committee of the Universidade do Vale do Sapucaí have reviewed and approved the study protocol (reference number: 113.612). Only those patients who agree to sign informed consent forms will be included in the study.

### Inclusion and exclusion criteria

Patients will be recruited from the private practices of the first three authors ([name], [name] and [name]). Women aged between 18 and 60 years who are candidates for breast augmentation with silicone implants via the inframammary fold approach will be eligible for the study. Patients with a body mass index (BMI) above 30 kg/m^2^, those on immunosuppressive therapy, those with diabetes, those who smoke, and those with a history of breast cancer or breast surgery will be excluded. Patients with an indication for an areolar or axillar approach and those who had the dressing wet will also be excluded.

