### Sample size

On the basis of the literature, an increase in bacterial growth of 100 colony-forming units (CFUs) per plate will be considered clinically significant [32]. For a statistical power of 95% and an alpha test risk of 5%, the sample size has been estimated to be 48 patients per study arm.

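### Excluding patients whose dressing got wet acts after allocation and, from day 1 on, only in group II, so the day-6 CFU comparison is not protected by randomisation and can be biased

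*Protocol article*

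**What the plan says.** Under Inclusion and exclusion criteria, after the baseline conditions, the protocol article adds that "those who had the dressing wet will also be excluded". No time limit is given and neither group is named.

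The sections on group assignment and on procedures fix the timing. The dressing goes on in the operating room. Then: "An opaque envelope with the patient number will be opened on the first postoperative day to reveal the allocation of the patient".

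- **Early removal (group I):** the dressing comes off at that visit and a swab is taken. On hygiene the article says: "The patient will be instructed to return to their normal personal hygiene routine". These patients come back on day six for a further swab.
- **Late removal (group II):** "If the patient is allocated to group II, she will be instructed to not wet the bandage for six days". Removal and the swab both fall at the end of that period.

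The primary outcome is the number of CFUs. Statistical analysis compares the two groups six days after dressing application with the Mann–Whitney U test, separately for each culture medium. Nothing says that patients with a wet dressing return to that comparison.

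**The concern.** The rule stands among the eligibility criteria but depends on something that happens during follow-up. From day 1 to day 6 a group I patient has no dressing to wet. She may wet the wound and stays in the trial. A group II patient who wets her dressing in the same five days is removed. The rule is neutral as written and one-sided in operation.

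Failing to keep gauze dry for six days is one of the things that can happen under the longer protocol, and the stated aim is to compare two protocols of wound care. If the patients removed differ in skin colonization from those who stay, the day-6 difference partly reflects who was removed. Once they are dropped without a day-6 swab, nobody can check whether that happened or in which direction. This is not a point left to an analysis plan: the article states the exclusion outright.

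**Working it through.** **1. Who can meet the criterion, and when**

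| Period | Group I | Group II |
|---|---|---|
| Surgery to envelope opening (day 1) | can meet it, allocation unknown | can meet it, allocation unknown |
| Envelope opening to day 6 | cannot: dressing removed, normal hygiene resumed | can meet it |

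Exclusions in the first row do not depend on allocation. Those in the second fall on one arm only.

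**2. The plan's own figure**

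The article gives a difference of 100 CFU per plate, 95% power, 5% alpha and 48 per arm, but no standard deviation. So 48 can be neither confirmed nor refuted. Solving n = 2·SD²·(z_alpha + z_power)²/difference² for SD gives:

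- two-sided: 100 × √(48/2) / (1.960 + 1.645) = 135.9 CFU
- one-sided: 148.9 CFU

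The two-sided value is used below only as a scale. The point does not depend on it.

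**3. Shift produced by the exclusion**

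Let w be the share of group II with a wet dressing and D the mean CFU in wet minus dry patients. The full group II mean is (dry mean) + w·D. Removing the wet patients therefore moves the group II mean by −w·D. Neither w nor D is in the article, so all values are assumptions:

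| w | D = −100 | D = 0 | D = +100 | D = +200 |
|---|---|---|---|---|
| 10% | +10 | 0 | −10 | −20 |
| 20% | +20 | 0 | −20 | −40 |
| 30% | +30 | 0 | −30 | −60 |

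A negative shift favours the six-day dressing.

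**4. Effect on the Mann–Whitney test, normal model**

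Simulation, 4,000 trials per setting, 48 per arm, SD 135.9, full randomised arms with equal means. Entries are the share of trials significant in favour of group II after the exclusion (about 2.5% expected):

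| w | D = −100 | D = 0 | D = +100 | D = +200 |
|---|---|---|---|---|
| 10% | 0.8% | 2.6% | 5.3% | 9.8% |
| 20% | 0.5% | 2.9% | 9.7% | 24.6% |
| 30% | 0.2% | 2.5% | 15.0% | 47.4% |

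For D = −100 the total error is 5.7%, 9.7% and 15.4%, nearly all favouring group I. With every randomised patient kept, the total error is 4.5–5.5% throughout.

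**5. Effect on the test, skewed counts**

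Negative binomial counts, mean 60 in dry patients, k = 0.8, capped at 300, no true difference. Being a patient who would wet a dressing is a personal characteristic present in both arms, and such patients are removed from group II only. Total false-positive rate:

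- 5% wet, threefold CFU: about 5%
- 10% wet, threefold: about 6%
- 20% wet, threefold: about 10–11%, nearly all favouring group II, with a spurious mean difference of about 16 CFU
- 20% wet, fourfold: about 13%
- 20% wet, half the CFU: about 7–8%, favouring group I

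**6. Same counts, different mechanism**

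If wetting itself raises counts, in group II only, and dressing duration has no other effect, the dry group II patients match group I. Rejection after exclusion is then 4.8% at 20% wet and threefold, and 4.2–5.3% over 5–20% wet and two- to fourfold CFU.

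**The case against.** A reader might infer that the comparison is definitely biased towards the six-day dressing. The article does not support that. It would require wet-dressing patients to have higher day-6 counts than dry ones, which is plausible but stated nowhere. Without a difference there is no bias, and with lower counts it reverses.

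A second objection is that the inflated false-positive rate depends on the mechanism, and this stands. The 10–11% arises if women who wet dressings carry more bacteria anyway. If wetting itself raises the count, the exclusion does not inflate the error for the question of dry six-day dressing versus early removal. It changes the question, and it hides a harm of the longer strategy as used. Either way, the full comparison of the two protocols is not what gets tested.

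Third, the effect may be small. At 5–10% wet and threefold CFU the error is close to nominal, and a spurious 16 CFU is well below the 100 CFU that the article calls clinically significant. This too stands: no wetting rate is given, and 20% is only an illustration.

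A reader might also infer a loss of power, since the sample size section says only that "the sample size has been estimated to be 48 patients per study arm". That does not follow. The article does not say whether excluded patients are replaced, recruitment was still open, and an attrition allowance may sit in the full protocol.

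None of this removes the structural point: after day 1 the rule can act in one arm only.

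**Conclusion.** The concern holds as a matter of structure. The article states a post-allocation exclusion that from day 1 can apply only to group II, and it bears on the day-6 comparison of the primary outcome. That comparison is between patients who kept the dressing dry for six days and essentially all group I patients. It can be biased, plausibly but not certainly in favour of the longer dressing.

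Size and direction rest on two quantities that the article does not give: the wetting rate, and the CFU level in wet-dressing patients. Over the assumptions shown, the effect runs from none, through a reversal, to a false-positive rate of about twice nominal (20% wet, threefold CFU as a patient characteristic), and higher under the more extreme normal-model settings. The article does not establish that any enrolled patient has been excluded for this reason. The change is worth making because it removes a possible bias at little cost.

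**What to change.** - Remove the wet-dressing item from the exclusion criteria as far as the analysis is concerned, and record wetting as a protocol deviation with its date.
- Take the day-6 swab wherever possible in every randomised patient, including group II patients whose dressing got wet or came off early.
- Make the primary analysis a comparison of all randomised patients in their allocated group.
- Show the dry-dressing set only as a labelled sensitivity analysis.
- Report the number of wet dressings by arm, including any among the 69 patients already enrolled. Any such patient whose day-6 swab exists belongs in the primary analysis.

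The cost is mainly wording. The day-6 sampling visit is already planned in both groups, but the article ties the group II swab to dressing removal on day six. Sampling patients with a wet or early-removed dressing therefore has to be arranged explicitly. The estimate will be for the strategy as used and may be slightly diluted compared with a dressing kept dry throughout. Dressing duration and care instructions do not change.
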